#### Enrollment and allocation

Interested respondents will complete the initial assessment using an online survey to determine whether they can participate in the study. In this survey, we will also ask eligible participants whether they would be able to pick up the smartwatch from an external institute and be willing to provide the smartwatch data for the duration of the study. Sending smartwatches to participants is not feasible due to requirements from the Cantonal Ethics Commission (Ethics Commission of the Federal State of Zurich, Switzerland) regarding anonymous data collection. Eligible respondents will be enrolled in the study and randomly allocated to either the intervention or waitlist control group using an algorithm on the website (www.bedda.me). If participants are interested in using a smartwatch, it is randomly decided whether they receive a smartwatch or not. Participants not allocated to the smartwatch group will receive instructions on downloading and installing the BEDDA app on their own. Participants assigned to the smartwatch group will receive instructions on how to book an appointment at an external organization to pick up their smartwatches. An individual from the external organization will help participants to install the app on the participantsâ€™ smartphones and enter the key of the smartwatch in the study app. We will collect no personal data during this process and cannot associate any personal data with the collected data.

Usually, blinding participants and staff is complex in most digital health intervention studies. Participants can easily realize if they are in the intervention group that uses a form of digital therapeutic or if they are in a control group (e.g., receiving standard of care or a sham intervention such as printed health information). However, we aim to address this problem by providing installation instructions for all groups after recruitment and only disclosing the intervention’s start time via a notification of BEDDA. However, the smartwatch groups will have a clear indication that they are in one of the smartwatch groups (intervention or waitlist). Still, we will neither disclose the allocation to the intervention or waitlist group to staff or participants in the smartwatch groups.

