**Method:**

Participants will interact with the digital intervention BEDDA consisting of a scripted conversational agent, the slow-paced breathing training *Breeze*, and actionable advice for different symptoms. The intervention comprises 30 daily interactions to be completed in less than 45 days. We will collect self-reports regarding mood, agitation, anhedonia (proximal outcomes; first objective), self-reports regarding depression severity (primary distal outcome; second and third objective), anxiety severity (secondary distal outcome; second and third objective), stress (secondary distal outcome; second and third objective), voice, and breathing. A subsample of 25% of the participants will use smartwatches to record physiological data (e.g., heart-rate, heart-rate variability), which will be used in the analyses for all three objectives.

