### Study design

Figure 8 shows the experimental design of the study. The study will run for 60 days, and participants will be randomly (using an algorithm on the recruitment website) allocated to one of four groups we listed in Table 1: intervention with smartwatch (IG_sw_), intervention without smartwatch (IG_nsw_), waitlist with smartwatch (WG_sw_), waitlist without smartwatch (WG_nsw_). The intervention part of the study will run for 30–45 days, depending on how many days the participant needs to finish the required 30 once-per-day guided interactions (described below). Participants allocated to the intervention group (IG_sw_ and IG_nsw_) will start the experiment first. In their first interaction (T_1_), they will receive the study information, give written informed consent via the app (type of content approved by the ethics committee), complete the initial assessment, receive a tutorial on how to use the app, and complete a training with Breeze for the first time. Participants allocated to the waitlist group (WG_sw_ and WG_nsw_) will complete the baseline assessment (T_0_) but will not yet start using the app for another 30 days. In these first 30 days, participants in the intervention group will interact daily with BEDDA. This interaction includes dialogues with the conversational agent, answering questions before and after Breeze, and conducting breathing training with Breeze. Each day, they can also choose whether they want to receive daily wisdom matching the symptom of the day. Additionally, the conversational agent moves the story further each day, and the app uses gamification elements to illustrate progress. On day 15 of the intervention, participants allocated to the intervention group will respond to the half-time assessment questions and on day 30, participants in the intervention group will respond to the final assessment.

**Table 1 Tab1:** Groups included in the study

Group	Treatment	Smartwatch	Planned N
IG_sw_	Intervention	Yes	25
IG_nsw_	Intervention	No	75
WG_sw_	Waitlist	Yes	25
WG_nsw_	Waitlist	No	75

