#### Incentive mechanism

Participants will receive financial compensation for their participation if they meet certain criteria. First, participants need to interact with the app at least once per day on 30 days and complete the daily trip with the intervention. The participants can use Breeze more often on any given day, but 30 different days are needed to complete the intervention and be eligible for compensation. Second, participants need to complete the additional questions at baseline (T_0_, waitlist control group only), the start of the intervention (T_1_), the half-time (T_2_), and the final assessment (T_3_) within the once-per-day guided interaction. Third, participants must complete the intervention in 30–45 days to receive a compensation of 40 CHF. Participants needing more than 45 days will not receive any financial compensation. Forth, participants completing the intervention in 30–40 days have the chance to win additional monetary compensation in a raffle (ten times 100 CHF, ten times 200 CHF, five times 300 CHF). Participants in the smartwatch group are not eligible for this raffle but can keep the smartwatch if they complete the intervention in 30-40 days. Since we are not collecting any personal information about the participants enforcing participants with insufficient data to return the smartwatch is not feasible. However, we strongly urge the participant in the final interaction to return the smartwatch if they did not provide sufficient data.

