For the second objective, we will proceed in a comparable matter. However, the dependent variables in these models are the symptom severity assessed by the PHQ-9 (depression), GAD-7 (anxiety), and TICS (stress). The independent variables remain the same (voice, breathing, physiological) with a potential extension of using the developed symptom markers from the second objective as additional independent variables. Due to only three assessment times (T_1_, T_2_, T_3_) resulting in three measurements for each participant, we will not be able to develop intra-subject models but will focus on generalizable models for the entire population. Similar to the second objective, we will also infer whether voice and breathing are complementary or alternative markers using a triangulation approach [95].

For the third objective, the estimation of efficacy, we differentiate between proximal and distal outcomes. We based this analysis on a the micro-randomized trial as introduced by Klasnja et al. [59]. However, we have the limitation that the outcomes measured are randomized and not the component. Therefore, we will use Generalized Estimating Equations (GEE; e.g., [96, 97]) to analyze the changes in proximal outcomes. Distal outcomes are the symptom severity changes as determined by the PHQ-9 (depression), GAD-7 (anxiety), and TICS (stress). As stated above in the section regarding sample size estimation, the primary distal outcome is symptom severity of depression. Due to this focus, our first analysis will be a two-way mixed ANOVA (2 groups $$\times$$ 3 measurement times). To investigate post-hoc, whether other factors such as belonging to the smartwatch group, age, and gender have an impact on a potential reduction of severity, we aim to use mixed effect linear regression (hierarchical groups such as intervention and smartwatch vs. no-smartwatch groups). In later analyses, we will investigate intercorrelations between the different dependent variables (PHQ-9, GAD-7, TICS) using a two-way mixed MANOVA (2 groups $$\times$$ 3 measurement times $$\times$$ 3 outcomes). We may compute additional MANOVAs comparing theoretically or empirically connected physiological outcomes to the three distal outcomes if physiological data allow such analyses.

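### The post-hoc smartwatch factor compares watch wearers with a group that includes people who were never in the watch draw, so it is confounded by willingness; the intervention-versus-waitlist comparison is not affected.

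*Protocol article*

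**What the plan says.** The protocol article describes the allocation twice. Under Study design, participants are randomly "allocated to one of four groups we listed in Table 1", with no condition attached. Table 1 plans 25 + 75 in the intervention arm and 25 + 75 in the waitlist arm, with and without a watch. The abstract gives the same share: "A subsample of 25% of the participants will use smartwatches to record physiological data".

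Enrollment and allocation gives the mechanics in two steps. For the arm, "Eligible respondents will be enrolled in the study and randomly allocated to either the intervention or waitlist control group". For the watch, the draw is conditional: "If participants are interested in using a smartwatch, it is randomly decided whether they receive a smartwatch or not". Before that, the screening survey covers ability to collect a watch: "we will also ask eligible participants whether they would be able to pick up the smartwatch from an external institute". The same survey question also covers agreement to share the data it records.

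Under Planned analysis, the third objective includes a mixed-effects regression: "To investigate post-hoc, whether other factors such as belonging to the smartwatch group, age, and gender have an impact on a potential reduction". The outcome is severity, and the grouping is described as intervention, and smartwatch against no-smartwatch. Willingness to take a watch is not mentioned, nor is a restriction to those who entered the draw.

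Watch recipients also differ in other ways. Under Incentive mechanism, "Participants in the smartwatch group are not eligible for this raffle". Instead, they may keep the watch if they finish in time. Under Enrollment and allocation, they get in-person help installing the app, while the others install it themselves.

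**The concern.** The watch is randomised only within the willing stratum, but the analysis as described uses everyone without a watch as the comparator. Willing people may differ from the rest in motivation, distance from the pick-up point or interest in self-tracking. Any such difference that also relates to change in PHQ-9 would be attributed to the watch. A reader who has only the Study design text and Table 1 would take the watch contrast as randomised across the whole sample.

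The stake is the interpretation of one secondary factor: whether wearing a watch changes the reduction in depression severity, or changes how well the intervention works. A valid randomised version of that contrast already exists inside the trial and would go unused.

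**Working it through.** **Reproducing the plan's figure.** Watch share from Table 1: (25 + 25)/(25 + 75 + 25 + 75) = 50/200 = 25%, which matches the abstract.

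**Inputs.**
- From the protocol: 50 participants with a watch and 150 without (Table 1); watches go only to people in the draw (Enrollment and allocation).
- Assumed, because the documents do not give them: W, the number of the 200 who are in the draw (called willing below); and Δ, the standardised difference in improvement between willing and other participants.

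**Composition of the comparator.** All 200 − W people outside the draw are in the no-smartwatch groups, so their share there is (200 − W)/150. The watch groups contain none of them.

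**Bias of a watch main effect when the watch does nothing.** Bias = Δ × (200 − W)/150. The false-positive rate uses a normal approximation at two-sided 5%, with SE = √(1/50 + 1/150) = 0.163 SD.

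| W willing | Share never in the draw | Bias, Δ = 0.2 / 0.3 / 0.5 SD | False-positive rate, Δ = 0.2 / 0.3 / 0.5 SD |
|---|---|---|---|
| 200 | 0% | 0 / 0 / 0 | 5% / 5% / 5% |
| 150 | 50/150 = 33% | 0.07 / 0.10 / 0.17 | 6.9% / 9.4% / 17.5% |
| 140 | 60/150 = 40% | 0.08 / 0.12 / 0.20 | 7.8% / 11.4% / 23.2% |
| 100 | 100/150 = 67% | 0.13 / 0.20 / 0.33 | 12.9% / 23.2% / 53.2% |

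**Arm-by-watch interaction.** The arm is randomised for everyone. With willingness balanced across arms, the share never in the draw is the same in both no-smartwatch groups: (100 − W/2)/75 = (200 − W)/150.
- If Δ is the same in both arms, the bias is Δ × (200 − W)/150 in each arm and cancels in the interaction.
- If Δ differs between arms by γ (willingness modifies the intervention effect), the interaction is biased by γ × (200 − W)/150.

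**Intervention versus waitlist.** All eligible respondents are randomised to arm, so willingness is balanced in expectation and this comparison carries no such bias.

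**After restriction to the draw.** Comparing 50 watch wearers with W − 50 willing people without a watch has no willingness bias by design. The effect detectable with 80% power is (1.960 + 0.842) × √(1/50 + 1/(W − 50)):
- W = 200: 0.46 SD
- W = 150: 0.49 SD
- W = 140: 0.49 SD
- W = 100: 0.56 SD

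The unrestricted contrast has 0.46 SD whatever W is. The precision lost is modest unless few people are willing.

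**The case against.** The strongest reply is that little depends on this contrast. It is a post-hoc factor listed beside age and gender, which nobody would read as randomised. The watch is a measuring device and not one of the three intervention components. The article nowhere calls the watch comparison randomised, its list of factors is open-ended, and covariates are commonly settled in an analysis plan that is not shown. If the model is meant to ask whether the intervention's benefit differs by watch group, a willingness difference common to both arms cancels. The two allocation descriptions can be read as overview and detail, and the different reward is openly disclosed.

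Much of this stands. It limits the point to a secondary analysis, and it shows that the main-effect bias does not carry over automatically to an interaction. It does not remove the point. An open covariate list does not repair a comparator that is described as the no-smartwatch groups as they stand. An interaction is protected only if willingness does not modify the intervention effect, which nothing in the article establishes.

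Two stronger readings are tempting and should not be drawn. A reader might infer that the trial's efficacy comparison is compromised; it is not, because the arm is randomised among all eligible respondents. A reader might also set a 0.20 SD bias against the 0.225 used in the sample size section and conclude that it matches the trial's target effect. That compares a watch contrast with an arm effect, and it rests on two assumed inputs. The label of the 0.225 is also doubtful: the stated 194 follows from reading it as Cohen's f with three groups, whereas reading it as d for two means gives 622.

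**Conclusion.** The point holds in a limited form. The watch draw is conditional on interest, the design overview omits that condition, and the post-hoc model as described does not account for it. A watch main effect is confounded by willingness, and an arm-by-watch interaction is confounded if willingness modifies the intervention effect.

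The direction and size of the bias cannot be determined from the documents. The 0.10 to 0.20 SD range assumes a 0.3 SD difference and 150 down to 100 willing of 200. The bias is zero if everyone is willing or if willingness is unrelated to improvement. Even the clean contrast estimates the effect of a package: the watch, a different incentive and in-person installation help. This is a cheap improvement to a secondary analysis and no threat to the trial's main conclusion.

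**What to change.** 1. Estimate the smartwatch factor, both main effect and arm-by-watch interaction, among participants who were in the watch draw, with arm in the model. Alternatively, keep the full sample and add willingness, plus willingness-by-arm when the interaction is estimated. If the model uses the repeated scores, so that an effect on reduction is a term with time, willingness must enter with the same time terms.
2. Keep the survey answer that determined entry to the draw and carry it with the allocation code into the analysis dataset. Data collection is anonymous and Table 2 lists no such variable, so this is best arranged before enrolment.
3. Reconcile the Study design text and Table 1 with the two-step allocation under Enrollment and allocation.
4. Describe the result as the effect of the smartwatch package: watch, different incentive and in-person installation help.

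Cost: no new question for participants, since the answer is already collected. There is one more variable to retain and link within the anonymous set-up. The restricted contrast is less precise: a detectable effect of 0.49 SD with 140 willing, or 0.56 SD with 100, against 0.46 SD for the unrestricted one.

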#### Daily interaction

Participants will be asked to interact with BEDDA by completing the once-per-day guided interaction (i.e., daily trip). Each daily interaction consists of different parts using the different elements of the intervention. Figure 9 illustrates such a daily interaction. First, the participants will interact with the chatbot and a treasure map showing the day's journey. Second, the participants will assess a subset of the Multidimensional Mood State Questionnaire (MDMQ) about their mood, agitation, and anhedonia [88, 89]. To reduce the burden on the participants, only one dimension of the MDMQ will be randomly selected each day. Figure 10 illustrates how the symptom of the day (e.g., symptom of the day is mood) and which version of the symptom of the day is presented in which order (e.g., Mood Version A is presented first, followed by Mood Version B after Breeze). One dimension consists of positive and negative items and has two versions with five items each. The participant will also indicate where they are conducting the breathing training (e.g., living room, office, etc.). Third, we will ask the participants to perform breathing training with Breeze. There, the app will instruct the participants to say three sentences to start the training: (1)“Lift the anchor.”, (2)“Set the sails.” (3)“Let's start today's journey.”. After this, participants will perform the breathing training. While sailing over the river, the participants will collect a bottle floating on the river. In this bottle, two items will be found the daily wisdom and one of the 30 keys. At the end of the exercise, participants will be instructed to read three sentences: (1) “Haul in the sails,” (2) “Set the anchor”, and (3) “I have finished today's journey.” Fourth, the participants will answer five different questions on the same MDMQ dimension as asked before the breathing exercise about either mood, agitation, or anhedonia. Fifth, the participants will provide a short indication of how accurately they perceived the detection of their breathing by responding to a question, adapted from Efendic et al. [90], with a seven-level response Likert scale ranging from “very inaccurate” to“very accurate”. Finally, they will be asked if they want to receive the wisdom collected on the way, showing the map of the completed journey and the number of keys they have accumulated in total.

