#### Voice and breathing sounds

We developed speech commands to capture commonly occurring and easily measured speech interactions. The commands are designed to be realistic in a setting outside of a study, meaning their length is similar to an interaction when giving commands to a voice assistant but also fit in the general story and setting of BEDDA. We implemented the voice commands in Breeze. To start and finish Breeze, the participants are visually instructed to say the three simple sentences before and after described above. Besides these voice interactions, we also derive the breathing sounds from Breeze. As the participant follows a guided breathing training each session with Breeze provides a set of inhalation, exhalation, and pause sounds.

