#### Audio features

From the different voice commands, we will extract different features reported in related work [16, 22]. We will extract vocal folds features (i.e., source features, e.g., jitter [%], shimmer [%], tremor [Hz]), vocal tract filter features (e.g. F_1_ mean [Hz], F_2_ mean), and prosodic features (i.e., melodic, e.g., F_0_ mean, F_0_ variability, intensity [dB]). We will approach the extraction of acoustic breathing features in a more exploratory way since less related work exists regarding breathing-based biomarkers for depression. For the analysis of breathing sounds, we plan to look at the spectrograms, MFCCs, and GTCCs of the recorded breathing sounds used in previous work [91, 92].

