## Planned analysis

We plan different analyses for the different research objectives, which we will describe in this section. This description cannot be holistic for the machine learning analyses (first and second objective), as we plan to explore different machine learning algorithms. For an initial overview, we aim to provide a distribution of the daily measured proximal symptoms and the measured distal severity. The choice of algorithms will depend on the observed performance of the resulting models. Regardless of the analysis, we will split the data into a training and a hold-out testing set. Using the training set, we will train and evaluate machine learning algorithms using cross-validation. This will allow us to compare machine learning algorithms, including different feature extraction pipelines, and determine which performs best. In a final step, we will use the hold-out test set to verify the cross-validation results by evaluating the resulting models on completely unseen data.

For the first objective, we plan to investigate different supervised regression models to predict mood, agitation, and anhedonia. We aim to use the following data sources: self-reported mood, agitation, and anhedonia (MDMQ), voice sounds, breathing sounds, reaction time, and physiological smartwatch data. Due to the availability of both features (voice, breathing, and physiological features) and labels (self-reported mood, agitation, and anhedonia), we will focus on supervised machine learning models. We aim to try different machine learning algorithms, such as but not limited to multivariate linear regression models, random forest, and multilayer perceptron models. We will also explore explained variance by the voice and breathing features in self-reported and physiological data using a triangulation approach [95] to determine whether DBMS can be used as an alternative or complementary assessment for symptoms of depression.

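### The start and end voice commands are different fixed sentences, so spoken text is fully confounded with pre/post-Breeze phase; pooled voice models that ignore phase can score partly on this

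*Protocol article*

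**What the plan says.** All references are to the Protocol article.

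- **Spoken text.** Daily interaction says of the start of a session that "the app will instruct the participants to say three sentences to start the training". The third of these is "Let's start today's journey". It then says: "At the end of the exercise, participants will be instructed to read three sentences". The third of those is "I have finished today's journey". The other two sentences in each set also differ. Single words recur (anchor, sails, journey), but no whole sentence appears in both sets. Voice and breathing sounds repeats the scheme: "To start and finish Breeze, the participants are visually instructed to say the three simple sentences before and after described above". Neither section describes rotation or a common sentence.
- **Label.** Each day one MDMQ dimension is drawn and measured once before and once after Breeze. The Fig. 10 legend and Proximal and distal outcomes describe a random, blocked draw of which version (A or B) comes first.
- **Features.** Audio features states: "From the different voice commands, we will extract different features reported in related work". It lists vocal-fold measures, first and second formant means, and prosodic measures including F0 and intensity.
- **Model.** For objective 1, Planned analysis states: "we plan to investigate different supervised regression models to predict mood, agitation, and anhedonia". Models are compared by cross-validation and then checked on a hold-out set. The section does not say whether start and end recordings are pooled, or whether phase enters the model or its evaluation.

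**The concern.** Formant means depend directly on which vowels are spoken, and F0 and intensity also vary with the phrase. Such features can therefore reveal which sentence set was spoken, and the sentence set reveals whether the recording was made before or after Breeze. The protocol expects the label to move between those two points: Breeze is included to improve symptoms, and the Background cites slow-paced breathing as improving mood. A pooled model could thus follow a chain from text to phase to label without the voice carrying any symptom information.

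The authors protected the questionnaire against this kind of link by counterbalancing its versions, but gave the spoken text no such protection. The hold-out set comes from the same sessions and would confirm the artefact. What is at stake is how the accuracy of a pooled voice marker for momentary mood, agitation or anhedonia can be read. Nor can a within-session change in voice be separated from the change of text, because no sentence is recorded at both ends.

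**Working it through.** **The plan's own figure.** The plan gives no within-session MDMQ shift and no performance target for the voice models. Its only correlation, 0.23 in Estimation of sample size, is described as the value needed with 194 participants, alpha 0.05 and power 0.80. By Fisher's z with two-sided alpha, r = tanh((1.960 + 0.842)/√(194 − 3)) = tanh(0.203) = 0.20, so 0.23 is not reproduced. That is a separate matter, and nothing below uses it.

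**Inputs.**
- Two recordings and two labels per session, one before and one after Breeze, so phase is balanced (Daily interaction).
- Sentence set and phase coincide in every session (Daily interaction; Voice and breathing sounds).
- Assumption: Breeze shifts the MDMQ mean by d within-phase standard deviations, with d from 0 to 0.8.

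**Correlation of a pure phase indicator with the label.** Set the within-phase label variance to 1. The indicator has variance 1/4, its covariance with the label is d/4, and the total label variance is 1 + d²/4. Hence

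r = (d/4) / (½ × √(1 + d²/4)) = d / √(d² + 4).

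| Assumed d | Calculation | r | r² |
|---|---|---|---|
| 0 | 0 / 2 | 0 | 0 |
| 0.2 | 0.2 / √4.04 | 0.10 | 0.01 |
| 0.3 | 0.3 / √4.09 | 0.15 | 0.02 |
| 0.5 | 0.5 / √4.25 | 0.24 | 0.06 |
| 0.8 | 0.8 / √4.64 | 0.37 | 0.14 |

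**Check by simulation with held-out participants.** Assumptions: 194 participants; 10 days per dimension (30 days × 2/6 from the block design); two recordings per day; intraclass correlation 0.5; 155 participants for training and 39 held out. One voice feature separates the two sentence sets by 3 SD and carries no mood information.

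| Assumed d | Hold-out r, pooled | Hold-out r, within phase |
|---|---|---|
| 0 | 0.00 | 0.00 |
| 0.2 | 0.09 | 0.00 |
| 0.3 | 0.13 | 0.00 |
| 0.5 | 0.20 | 0.00 |
| 0.8 | 0.31 | 0.00 |

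The pooled values fall below the closed form because this feature identifies phase imperfectly. Its correlation with phase is 3/√(9 + 4) = 0.83, and 0.83 × 0.37 = 0.31. The closed form is therefore the value for a perfect phase indicator.

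**The case against.** The strongest reply is that the harm depends on an analysis the article does not describe. Sentence identity helps only a model that pools start and end recordings, pairs each with its adjacent MDMQ score and ignores phase. The article says its machine-learning description is incomplete, and handling of phase may be set out in a fuller plan. This stands: the confounding is a fact of the design, but its effect on accuracy is conditional.

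Other parts also stand. The size of d is unknown, and at 0.2 SD the artefact explains about 1% of variance. Breathing sounds, reaction time and smartwatch data do not depend on the spoken text. The efficacy analysis of the MDMQ by GEE does not use voice, and no within-session voice-change analysis is planned. Finally, matching the sentences would not remove every phase effect, since the exercise just completed may itself alter the voice.

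The reply does not dispose of the point. The spoken text is a data-collection choice that this document fixes. Analysis within phase removes the pooled artefact, but no analysis can recover a text-matched comparison between the two ends of a session.

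**Conclusion.** The point holds in conditional form. Spoken text and phase coincide completely by design. If recordings are pooled without conditioning on phase, and if Breeze shifts the MDMQ mean, voice features can gain an apparent correlation of up to 0.10 at d = 0.2, 0.15 at 0.3, 0.24 at 0.5 and 0.37 at 0.8, with none at d = 0. These shifts are assumptions. The artefact adds to any real signal and does not create between-person or between-day signal within one phase.

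A reader might infer three stronger conclusions that the document does not support.

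- *Reported accuracy will necessarily mix symptom signal with sentence identity.* Pooling is neither planned nor ruled out.
- *The marker could not transfer to other speech because of this confounding.* Six fixed, command-like phrases limit transfer whether or not they are counterbalanced, and genuine within-phase signal may exist.
- *The artefact alone would reach the 0.23 in the sample-size section.* That requires a shift of about 0.47 SD, which the document does not give, and a perfect phase indicator. In addition, 0.23 is a detectable correlation for 194 participants and not a performance target for models of repeated recordings.

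**What to change.** 1. **Script.** Include at least one common sentence at both ends and base any start-versus-end voice comparison on it. Alternatively, randomise per session which set comes first, as is already done for the MDMQ versions. Either way, text is no longer tied to phase in the recordings compared.
2. **Analysis.** Do this in either case, and necessarily if the script is frozen: fit or evaluate the voice models within phase, and report any pooled model as gain over a benchmark containing only the pre/post indicator. The script change alone is not enough, because the breathing exercise may also alter the voice.

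The cost is a slightly less coherent storyline for the script change, or about half the recordings per model if models are fitted separately by phase. Neither step needs extra participants or procedures.
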